#### Data collection and sample handling

The overall study design is depicted in Fig. 1. Assessment of participants will be conducted at the perioperative (baseline = week 0), pre-treatment (week 3), post-treatment (week 15), and in each chemotherapy cycle. The primary outcomes will be the differences in the microbiota composition at different CRC tumor sites and differences in gut microbiota composition, adverse reactions, and blood concentration of capecitabine in patients with CRC treated for 12 weeks with XOS or placebo. The secondary outcomes will include blood indicators (hepatic and renal function, blood glucose, blood lipid, and inflammatory cytokines), SCFAs concentration, QoL, and mental health.

#### Gut microbial composition

Tissue samples including tumor, para-carcinoma mucosa (2 cm away from the tumor), and normal mucosa (as far as possible from the tumor) will be obtained from LSCRC and RSCC participants during surgery. Each tissue will be cut into small pieces with a volume of 1 cubic centimeter and put into the cryopreserved tubes. After being frozen in liquid nitrogen, the tissue will be stored in the − 80 °C refrigerator for later use.

The collection of feces will be carried out 24 h before or after blood sample collection on the day of ending the treatment. A total of 6 g stool samples from each participant will be collected in the morning for intestinal flora examination at baseline prior to preoperative bowel preparation and at 3 weeks (pre-treatment) and 15 weeks (post-treatment). Briefly, participants will be instructed to (1) exhaust urine before placing disposable stool tray to prevent contamination of stool, (2) pass stool on the tray, and (3) use a sterile spoon to dig up about 2g stool from middle and posterior segment of stool and inserted into a sterilized screw cap containers marked with the participant’s code and sampling date. For the purpose of reducing the change of microbiota composition in the stools, samples will be temporarily stored in a foam box with ice packs and transferred to the – 80 °C refrigerator in the laboratory within 2 h. The collection of feces will be carried out at the residence, and the patients will bring it to the researcher in the hospital.

The total DNA of frozen samples will be extracted via QIAamp (QIAGEN) stool DNA kit according to manufacturer’s instructions. DNA integrity and size will be assessed by the NanoDrop ND-1000 spectrophotometer (Thermo, USA) and 1% agarose gel electrophoresis. DNA samples will be kept at – 80 °C for later use. The bacterial 16S rRNA V3–V4 regions will be amplified by polymerase chain reaction (PCR). High-throughput sequencing will be performed on an Illumina platform.

A sequence similarity threshold of 97% will be used to select operational taxonomic units (OTUs) and then perform taxonomy assignments via the Usearch platform (version 7.1 http://drive5.com/uparse/). Principal coordinates analysis (PCoA) on weighted UniFrac distances will be measured on all OTUs by QIIME. Alpha diversity will be calculated through the Shannon index, Simpson index, and Chao1 metrics using mothur (version v.1.30.1 http://www.mothur.org/wiki/Schloss_SOP#Alpha_diversity). Linear discriminant analysis (LDA) will be performed on the analysis software LEfSe (http://huttenhower.sph.harvard.edu/galaxy/). Subsequently, the communities or species that have significant differences in the sample division will be selected.

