### Information questionnaires and physical evaluation

The personal information of the subjects will be conducted through basic information questionnaires, including body mass index, age, gender, and dietary habit. And these data were obtained in the form of an interview. Meanwhile, physical examination (height, weight, blood pressure, heart rate, etc.) is performed before the allocation.

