#### Data analysis

The visiting time of the participants is in accordance with the treatment course, so as to facilitate the retention of the participants. The measured data for each visit will be collected on paper and then recorded electronically on a secure, locked office computer. The paper version of the data will be locked in a bookcase. Only the investigators running in the study will have access to the final study dataset.

The obtained data will be analyzed by the SPSS software V26.0 (IBM, USA). Continuous data will be expressed as mean ± standard deviation (SD), and categorical data will be expressed as the number of cases (*n*) and percentage (%). Differences in parameter continuous variables and asymmetric variables between groups will be analyzed through independent samples *t* test and Mann-Whitney *U* test, respectively, using a paired *t* test to assess the effect of the intervention in each group. The normality of data will be assessed using the Kolmogorov-Smirnov test.

The results will be regarded as statistically significant if *p* values< 0.05.

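### Microbiota composition is a primary outcome twice, but the stated analysis contains no test of composition and ends in a selection of significant taxa without multiplicity control

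*Protocol article*

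**What the plan says.** Under Data collection and sample handling, the primary outcomes are "the differences in the microbiota composition at different CRC tumor sites and differences in gut microbiota composition, adverse reactions, and blood concentration of capecitabine". Two of these four items are microbiota composition: one compares tumour locations, the other compares XOS with placebo.

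The section Gut microbial composition fixes the methods down to software versions:

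- Ordination: "Principal coordinates analysis (PCoA) on weighted UniFrac distances will be measured on all OTUs by QIIME".
- Diversity: "Alpha diversity will be calculated through the Shannon index, Simpson index, and Chao1 metrics using mothur".
- Taxa: "Linear discriminant analysis (LDA) will be performed on the analysis software LEfSe".
- Decision rule: "Subsequently, the communities or species that have significant differences in the sample division will be selected".

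The same section provides for three tissues per patient ("Tissue samples including tumor, para-carcinoma mucosa (2 cm away from the tumor), and normal mucosa") and for stool at baseline, week 3 (pre-treatment) and week 15 (post-treatment).

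The Data analysis section names the independent-samples t test and the Mann-Whitney U test between groups, and a paired t test within each group for the effect of the intervention. It gives one criterion: results are "statistically significant if *p* values< 0.05".

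Randomisation is 1:1 within each tumour location. Baseline questionnaires record "body mass index, age, gender, and dietary habit".

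**The concern.** A primary outcome needs a stated step that can answer it. Here the ordination shows where samples lie but does not test whether groups differ. The diversity indices summarise richness and evenness: two communities with entirely different taxa can share one Shannon index. What remains is a taxon-by-taxon screen, whose output is a list and not an answer to whether composition differs.

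Two further features weaken that list. Nothing stated limits the number of false entries. And for XOS versus placebo, the pre-treatment sample enters only through a comparison within one arm, where change over the 12 weeks reflects chemotherapy as well as any supplement effect. The left-right contrast is not randomised, yet only unadjusted two-sample tests are named for it.

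At stake is whether the trial can report a conclusion on two of its four primary outcomes, or only a set of taxa whose reliability cannot be judged.

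**Working it through.** **1. Is there a figure in the plan to reproduce?** None for microbiota. The Sample size calculation section says that a flora endpoint could not be determined and relies on adverse effects in an earlier trial: 20 per group, 90% power, alpha 0.05. It gives no effect size, so this cannot be reproduced. For a two-sided comparison of means it would imply a standardised difference of (1.960 + 1.282) × √(2/20) = 1.025. That says nothing about power for composition.

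**2. Stated methods against the two questions.**

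| Stated step | Tests composition? | Controls false positives? |
|---|---|---|
| PCoA on weighted UniFrac | No test named | Not applicable |
| Shannon, Simpson, Chao1 | No, diversity only | No, three indices |
| LEfSe, then selection of taxa | Taxon by taxon | None stated |
| t / Mann-Whitney between groups | Single variables only | None stated |
| Paired t within arm | Single variables, no between-arm contrast | None stated |

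No row gives one between-group answer on composition.

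**3. Expected false taxa, if 0.05 applies to the screen.** The number of taxa is not given and is assumed here. With m null taxa, the expected number of false selections is 0.05 × m: 2.5 for 50, 5 for 100 and 10 for 200. No LDA cut-off is applied.

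**4. Share of selected taxa that are false.** With a fraction π of taxa truly different and power w per taxon, the share is 0.05(1 − π) / [0.05(1 − π) + πw]. Assume 25 per arm and a standardised difference of 0.8, so that w = 0.807:

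- π = 5%: 0.0475 / (0.0475 + 0.0404) = 54%
- π = 10%: 0.0450 / (0.0450 + 0.0807) = 36%
- π = 20%: 0.0400 / (0.0400 + 0.1614) = 20%

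Over standardised differences from 0.5 to 1.025 and the same values of π, the range is 17% to 69%.

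**5. Effect of false-discovery control.** Simulation with 1,000 runs, 100 independent normal taxa, 10% truly different at 0.8, t tests:

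| Per group | Rule | False taxa | False share | Sensitivity |
|---|---|---|---|---|
| 25 | p < 0.05 | 4.4 | 35% | 79% |
| 25 | Benjamini-Hochberg 5% | 0.2 | 5% | 35% |
| 50 | p < 0.05 | 4.5 | 30% | 98% |
| 50 | Benjamini-Hochberg 5% | 0.5 | 4% | 86% |

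The 50-per-group rows correspond to left versus right, or to XOS versus placebo with locations combined.

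Steps 3 to 5 are illustrations. Real taxa are correlated, so figures based on independence are indicative only.

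**The case against.** The strongest reply is that this is a condensed article. LEfSe thresholds, a false-discovery method, covariates and a distance-based test beside the ordination are commonly left to a full protocol or SAP, and nothing in the text excludes them. That stands as far as mere silence goes. It does not cover what is stated: a significance-based selection rule for primary outcomes, one blanket threshold, and named between-group and within-arm tests. A later plan would have to replace that wording, not just add detail.

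Several stronger readings are tempting, and the document does not support them:

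- *That LEfSe is set at p < 0.05.* The threshold stands in Data analysis, beside the SPSS tests. Carrying it to LEfSe is an inference, and an LDA cut-off could shorten the list.
- *That baseline is ignored.* Week-3 stool is collected and a paired test is named. What is not stated is a between-arm comparison that uses it.
- *That location is ignored.* The grouping used for taxon selection is not defined and might be by location. The named between-arm tests, however, make no use of the strata.
- *That XOS versus placebo is confounded.* It is randomised within location, so adjustment there serves precision. Confounding concerns left versus right only. One can argue that this aim is descriptive, but it is listed as primary, and diet is named in the article as interfering with gut microbiota.
- *That the three tissues inflate the error rate.* Treated as independent, with assumed within-patient correlation ρ of 0.3, 0.5 or 0.7, the design effect 1 + 2ρ is 1.6, 2.0 or 2.4, and a nominal 5% test would have a true error of 12%, 17% or 21%. No section says that tissues will be pooled this way, so this is a caution and not a measured defect.

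**Conclusion.** The point holds in a bounded form. For two of four primary outcomes, the stated analysis has no community-level test and ends in a selection of taxa without stated error control. The between-arm tests that are named use neither the week-3 sample nor the randomisation strata.

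Its size depends on assumptions. If 0.05 governs the screen, about 5 false taxa per 100 null taxa are expected. Among selected taxa, the false share at 25 per arm runs from 17% to 69% over the scenarios tried. A reader might infer that the taxon results will be largely uninterpretable, or that a list will emerge whatever the truth. Neither is shown: the number of taxa, the proportion truly different and any LDA threshold are all unstated.

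**What to change.** Pre-specify one community-level test per question on the weighted UniFrac distances already planned. PERMANOVA is one suitable choice among several.

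1. **Tumour location.** Tumour tissue, one sample per patient, left versus right, adjusted for the recorded age, sex, BMI and dietary habit, because location is not randomised.
2. **XOS versus placebo.** Stool, comparing arms on the change from week 3 to week 15 (the treatment-by-time term), with treatment labels permuted between patients within tumour location.

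Report taxon-level results as exploratory, with Benjamini-Hochberg control of the false-discovery rate and, for the treatment contrast, the week-3 value as covariate. Keep PCoA and LEfSe as descriptive displays. Wherever tissues from the same patient are analysed together, account for the patient.

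The cost is wording and analysis code; no new samples or patients are needed. The downside is real: fewer taxa will be called significant. In the illustration above, sensitivity fell from 79% to 35% at 25 per arm and from 98% to 86% at 50 per group. That is a further reason to rest the primary conclusion on the community-level test and not on the taxon list.

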#### Stool SCFA profiling

Stool sample aliquots of 50 mg g of dry weight each will add with 50 μL phosphoric acid, 100 μL isohexanoic acid solution, and 400 μL diethyl ether to homogenize. After centrifugation, the supernatant will be separated for gas chromatography-mass spectrometry (GC-MS) analysis. Stool SCFA profiling will be conducted using an Agilent Technology 6890 GC with autosamplers and 5973 MS Detection and Chemstation Data System (Agilent, Singapore). Chromatographic conditions will be as follows: Agilent HP-INNOWAX capillary column (30 m × 0.25 mm ID × 0.25 μm); shunt injection, injection volume 1μL, shunt ratio 10:1; injection port temperature of 250 °C; ion source temperature of 230 °C; initial oven temperature of 90 °C, 10 °C/min up to 120 °C, 5 °C/min up to 150 °C, 25 °C/min up to 250 °C, and keep at 250 °C for 2 min. Helium will be used as gas carrier at a constant flow rate of 1 mL/min.

#### Blood tests

Venous blood samples will be collected before preoperative bowel preparation, at 3 weeks (pre-treatment) and 15 weeks (post-treatment). After fasting for 12 h, venous blood will be collected into a coagulating tube in the morning and centrifuged at 3000 rpm for 10 min for obtaining the upper serum (Thermo, USA). In addition to some of the usual blood biochemical indexes, we will use commercial enzyme-linked immunosorbent assay (ELISA) kits to assess the levels of inflammatory cytokines, including tumor necrosis factor-α (TNF-α), interleukin-1β (IL-1β), and interferon gamma (IFN-γ). Cellular immune indices, including T lymphocytes (CD3+), helper inducer T cells (CD3+CD4+), and suppressor/cytotoxic T cells (CD3+CD8+), will be measured by BD-FACS Canto II flow cytometer (Becton Dickinson, USA).

For the purpose of evaluating the bioavailability of chemotherapy drugs in participants, the blood concentration of capecitabine will be measured at 15 weeks (after intervention). On the third day of the fifth cycle of treatment (taking capecitabine for at least four meals), 5 mL venous blood samples will be collected 2 h after taking medicine in the morning, put into a tube with ethylene diamine tetraacetic acid (EDTA) anticoagulant, and sent to the pharmacy department of the hospital for testing immediately.

#### Adverse effects

Adverse effects, including nausea, vomiting, diarrhea, leukopenia, anemia, thrombocytopenia, diarrhea, oral mucosal reaction, peripheral neuropathy, hand-foot syndrome, pigmentation, and abnormal liver function, will be assessed in each chemotherapy cycle using the Common Terminology Criteria for Adverse Events (CTCAE) version 5.0 [40]. Patients will be informed of the types of all adverse effects prior to the start of the experiment. After the beginning of the experiment and before each chemotherapy treatment, all adverse effects will be questioned and recorded from grades I to IV according to severity in the office. There is no knowledge of the possibility of any discomfort or adverse event with this supplementation. Participants are asked to inform the investigators in time if there is any adverse event that may be associated with prebiotics. These adverse events will be recorded by investigators. Protocol modifications will be communicated to the ethics committee through an official modification request, and the participants will be notified by telephone.

#### Food guidance and records

The patients have the dietary pattern according to the nutrition guidelines for patients with colorectal cancer by the European Society for Clinical Nutrition and Metabolism (ESPEN) [41]. In order to minimize the interference of personal diet on the gut microbiota and record changes in dietary habits in time, volunteers will be asked to complete a 72-h food record each time a stool sample is collected. Before completing the food record, food record forms with filling instructions and food-weighing electronic scales will be distributed to patients in advance. The professionals will also teach them how to fill out forms. They need to describe all foods and beverages consumed in detail including ingredients, weight, and cooking style. Daily nutrient intakes will be calculated based on the China Food Composition 2009 [42].

#### Health-related QoL

QoL will be assessed in each chemotherapy cycle using Chinese version of QoL questionnaire-caner 30 (QLQ-C30) formulated by the European Organization for Research and Treatment of Cancer. The questionnaire has 30 items, including 5 functional scales, 3 symptom scales, 6 individual measures items, and a global health [43].

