## Objectives

Firstly, this study aims to explore the difference of tumor microbiota and the different gut microbiota changes during treatment between LSCRC and RSCC. Moreover, another goal of the trial is to investigate the effect of XOS on (i) increasing the bioavailability of cytotoxic drug, (ii) reducing the adverse effects of chemotherapy, and (iii) improving the QoL of CRC patients by modifying gut microbiota.

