**Table 1 Tab1:**
[figure not shown]
SPIRIT diagram: schedule of enrollment, interventions, and assessments

*The experiment takes 12 weeks, and every cycle of chemotherapy takes 3 weeks

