#### Mental health

The prevalence of anxiety and depression in CRC patients is 13–57% [44], and one of the important factors is the adverse effects of chemotherapy [45]. Hospital Anxiety and Depression Scale (HADS), an effective questionnaire with 14 items, will be used to assess depression and anxiety in each chemotherapy cycle. Each item is on a 4-point scale and final scores are proportional to the degree of anxiety and depression.

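### A multi-scale, repeatedly measured quality-of-life aim has no named contrast, and the only stated tests are single comparisons at an unadjusted 0.05

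*Protocol article*

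**What the plan says.** The Objectives of the protocol article list three intended effects of XOS. The third is "improving the QoL of CRC patients by modifying gut microbiota". Under Data collection and sample handling, the secondary outcomes end with "SCFAs concentration, QoL, and mental health", so QoL is an aim but not a primary outcome. Mental health is a secondary outcome and is not among the aims.

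The Health-related QoL section describes the instrument: "The questionnaire has 30 items, including 5 functional scales, 3 symptom scales, 6 individual measures items, and a global health". It is completed in each chemotherapy cycle. The Mental health section says that HADS "will be used to assess depression and anxiety in each chemotherapy cycle". The note to Table 1 gives the time frame: "The experiment takes 12 weeks, and every cycle of chemotherapy takes 3 weeks".

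The Data analysis section names an independent-samples t test or a Mann-Whitney U test between groups, and a paired t test within each group to assess the intervention. It then gives one rule for everything: "The results will be regarded as statistically significant if" p is below 0.05. It names no QoL scale, time point or summary, and no method for repeated scores.

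**The concern.** A QoL claim is intended, because QoL stands beside bioavailability and adverse effects as something XOS is meant to improve. The stated analysis does not fit the data collected to support it.

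- **Many scores.** The questionnaire gives 15 scores, and the stated rule lets any of them count as significant at 0.05.
- **Repeated scores.** They are collected every cycle, but each stated test takes one comparison at a time. The plan therefore gives no single estimate of the treatment effect over the course.
- **Within-arm tests.** A paired test in one arm shows change over time. It does not compare XOS with placebo.

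At stake is whether a statement that XOS improves QoL would rest on one contrast chosen in advance, or on whichever scale or cycle happened to cross the threshold.

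**Working it through.** **Inputs from the protocol article**
- QLQ-C30 scores: 5 + 3 + 6 + 1 = 15 (Health-related QoL).
- Cycles in the intervention: 12 weeks / 3 weeks = 4 (note to Table 1). Blood tests also mentions a fifth cycle, which is not counted here.
- Threshold: 0.05 with no adjustment (Data analysis). Sidedness is not stated. Two-sided is assumed, which puts 2.5% in the direction favouring XOS.
- The article gives no overall error rate for QoL, so there is no figure to reproduce. Its sample size rests on adverse effects (20 per group, 90% power), not on QoL.

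**Assumption.** The correlation r between test statistics is not in the document. A common r is used, with 0.5 as the central value and a range from 0.9 to 0.

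**Formula.** For m tests with no XOS effect, φ and Φ being the standard normal density and distribution function:

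P(at least one p < 0.05 favouring XOS) = 1 − ∫ φ(u) · [Φ((1.96 − √r·u) / √(1 − r))]^m du

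At r = 0 this is 1 − 0.975^m. For a difference in either direction, the bracket becomes Φ((1.96 − √r·u)/√(1 − r)) − Φ((−1.96 − √r·u)/√(1 − r)), and at r = 0 the result is 1 − 0.95^m.

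| Tests | r | Favouring XOS | Either direction |
|---|---|---|---|
| 15 scales, one time point | 0.9 | 7% | 14% |
| | 0.5 | 18% | 36% |
| | 0 | 1 − 0.975^15 = 32% | 1 − 0.95^15 = 54% |
| 15 scales × 4 cycles = 60 | 0.9 | 10% | 20% |
| | 0.5 | 34% | 66% |
| | 0 | 1 − 0.975^60 = 78% | 1 − 0.95^60 = 95% |

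Adding two HADS scores at four cycles (60 + 8 = 68 tests) gives 35% favouring XOS and 69% in either direction at r = 0.5.

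**Second check.** This was a simulation of t tests with no effect: 50 versus 50 patients, 2,000 runs, assumed correlations of 0.3 to 0.7 between scales and 0.5 to 0.7 between cycles. For 15 scales it gave 14% to 23% favouring XOS at one time point, and 28% to 52% over four cycles. The either-direction figures were 28% to 46% and 55% to 88%.

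**Precision.** The variance of a four-visit mean relative to one visit is (1 + 3r)/4, with r here the within-patient correlation. It is (1 + 1.5)/4 = 0.625 at r = 0.5 and (1 + 2.1)/4 = 0.775 at r = 0.7.

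**The case against.** The strongest reply is that this is a condensed article. The choice of a deciding scale, a time point and multiplicity handling for secondary outcomes commonly sits in a statistical analysis plan, which is not shown. That stands for the omissions taken alone, and formal ordering or a Holm procedure across secondary outcomes is a matter of preference. It does not dispose of the point, because the Data analysis section is not silent. It states single-comparison tests, within-arm paired tests and one unqualified threshold, and an analysis plan faithful to that text would inherit the mismatch.

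Three stronger readings are tempting, and the document does not support them.

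- **That every scale will be tested at every cycle.** The article says the questionnaires are completed each cycle. It does not say each score is tested each cycle, so the 60-test figures are conditional.
- **That a false claim of benefit is more likely than not.** The 66% and 69% count results in which XOS worsens QoL, and those cannot support a claim of improvement. Counting only results in favour of XOS gives 34% and 35% at a correlation of 0.5. The chance passes one half only if all cycles are tested and the correlations are weak.
- **That mental health is an aim of the same standing.** Only QoL is named in the Objectives.

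It is also fair to say that an average over cycles and an end-of-treatment score answer different questions, and neither is an error. The precision gain compares the average with a single-visit analysis that the plan does not name either.

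**Conclusion.** The concern holds in limited form. For a named secondary aim measured by 15 scores in every cycle, the stated analysis is a poor fit: it has no repeated-measures element, it relies partly on within-arm tests, and it applies an unadjusted 0.05 throughout.

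With no XOS effect, the chance of at least one nominally significant result in its favour is about 18% at a single time point (7% to 32%). It is about 34% (10% to 78%) if all four cycles are also tested. The nominal figure is 2.5%. These sizes rest on assumed correlations, two-sided testing and arms pooled over tumour location. Over the whole range the chance exceeds the nominal level.

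The primary outcomes are not affected. The change is worth making before unblinding, since a scale or cycle chosen afterwards could not be defended as planned.

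**What to change.** In Data analysis, name one QoL contrast: QLQ-C30 global health status, XOS versus placebo, estimated over the treatment cycles in a repeated-measures mixed model. Use the pre-treatment score and tumour location as covariates; randomisation is already done within location. Let this replace separate per-visit tests and within-arm paired tests for QoL.

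State which questionnaire supplies the pre-treatment score. Randomization and blinding mentions baseline questionnaires without naming them, so confirm that the QLQ-C30 and HADS are among them or are completed before the first dose.

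Analyse HADS in the same way as a secondary outcome. Report the other QLQ-C30 scales and all single-cycle comparisons as exploratory estimates with 95% confidence intervals, without claims of significance.

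The cost is a few sentences of text and a mixed model that the planned SPSS version can fit. If the pre-treatment score is confirmed, no new data are needed. The small downside is that an isolated scale or cycle with p < 0.05 can no longer be claimed as a QoL benefit.
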